#### Sample size considerations and statistical analyses

The study has four primary endpoints; multiplicity over the primary endpoints will be protected by a fixed testing procedure. First, the non-inferiority of the 500 mg vs. 1000 mg at three months will be tested at *p* < 0.05 (two-sided). If this is statistically significant, then 500 mg vs. 1000 mg will be tested at *p* < 0.05 (two-sided) at six months. If that is statistically significant, then 200 mg vs. 1000 mg will be tested at *p* < 0.05 (two-sided) at three months and if that is statistically significant, the last test will be 200 mg vs. 1000 mg at *p* < 0.05 (two-sided) at six months. As we have four primary endpoints, we aim to have enough power for each at 95% for an NI margin of δ = 0.6. Under the worst-case scenario that these four are not correlated (the expectation is that they are positively correlated, see Table 1) and that the intervention is indeed non-inferior to the control condition, then the overall power for rejecting the null hypothesis of inferiority on all four is at least 95% × 95% × 95% × 95% = 81%. We calculated the sample size for one endpoint (e.g. the comparison of 500 vs. 1000 mg at six months). For 2:1 randomisation and a non-inferiority test assuming the true difference between treatments is 0, the total sample size for a t-test having a power 1-β when testing at significance level α (two-sided) and a non-inferiority margin δ is Ntot = (4.5)^2^ × (z_1-α/2_ + z_1-β_)^2^ × SD^2^/δ^2^, where z denotes the normal quantiles which are correct for non-small sample sizes. When correction for baseline is incorporated, this sample size is reduced by (1-r^2^) where r is the correlation in DAS28 between baseline and follow up (formula 7 with n = 1, π_0_ = 1/3, π_1_ = 2/3, and section 2.3 of Teerenstra S, et al. [36]). Note that the two groups then have sizes Ntot/3 and 2 × Ntot/3. To determine the correlation r between baseline and follow-up measurement of the DAS28, the following assumptions were used. Baseline DAS28 has a SD = 0.7 and the change from baseline to three (or six months) has a standard deviation of SDchange = 0.6 based on data from an earlier dose reduction trial [37]. As SD^2^change = 2 × (1-r) × SD^2^, it follows that r = 0.63. Then a total trial size of 80 participants would be enough. Table 1 illustrates the total trial size when the correlation between endpoints is smaller than anticipated.

**Table 1 Tab1:** Total trial sample size at various correlations between endpoints

SD change	r	Sample size 1000 mg arm	Total trial size (5 x sample size in 1000 mg arm)
0.9	0.17	26	130
0.8	0.35	24	120
0.7	0.5	20	100
0.6	0.63	16	80

To protect for a too optimistic correlation, we therefore choose a total trial size of 130 and this is further increased to 140 patients to account for patient drop-out.

Primary analyses will be done per protocol (PP), as this is the most conservative approach for a non-inferiority study. In addition, analyses will be performed on an intention-to-treat basis (ITT). For PP analysis, we will include patients who have received the study medication and completed follow-up of six months or until treatment failure (and last observation of disease activity carried forward).

The primary endpoints will be tested using 95% confidence intervals based on linear regression with the change in DAS28-CRP as outcome, dose group as determinant and baseline values of DAS28-CRP as covariate (ANCOVA).

To find predictors (including age, sex, disease duration, RF/ACPA status, CD19+ B-cell count, serum RTX, serum anti-RTX), patients will be categorised into responders (DAS28-CRP < 2.9 at six months and no treatment failure) and non-responders (all other patients). The absolute number (and thus also proportion) of responders will determine the number of predictors that is admissible for analysis, according to the rule of ten-events-per-variable given that predictors are predetermined. Univariate logistic regression analysis will be performed for the admissible predictive factors, with a deliberately liberal *p* < 0.20 as selection criterion. Univariately significant variables are entered in a full multivariate logistic regression model, that is step-wise reduced until all *p* < 0.20. Internal validation and shrinkage will be performed using a bootstrapping procedure with 1000 repetitions. Performance of the multivariate predictive model will be evaluated using discrimination (area under the receiver operator curve) and calibration (calibration slope, calibration plot and Hosmer-Lemeshow test).

Costs will be calculated and quality-adjusted life-years (QALY) will be based on EuroQol-EQ5D-5 L utility scores. Decremental cost-effectiveness analyses (CEA) will be performed using bootstrap analyses; incremental net monetary benefit (iNMB) will be used to express cost-effectiveness at different willingness-to-pay (WTP) values in the range of €20,000–80,000 per QALY.

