### Objectives

The primary objective of the REDO trial is to compare the difference in efficacy between two ultra-low doses (1 × 200 mg and 1 × 500 mg) and standard low dose (1 × 1000 mg) of RTX retreatment on the change in DAS28-CRP, compared to a pre-specified non-inferiority margin of 0.6 DAS28 points, at three and six months. Therefore, the study has four primary endpoints. Although we are aware that patients are sometimes treated with longer intervals than six months, showing non-inferiority at six months is relevant, for ultra-low RTX dose with at least six-month intervals is still a lower cumulative dose as standard low-dose 1000 mg every 9–12 months.

The main secondary objectives are: to assess the difference in efficacy between the two ultra-low dose interventions for the same outcomes; to compare the proportion of patients with a DAS28-CRP < 2.9 (low disease activity), DAS28-CRP < 2.4 (remission) and remission according to Boolean ACR/EULAR criteria at three-month and six-month follow-up; to assess the between-group differences in the change in functioning (HAQ-DI) and quality of life (EQ5D-5 L); and to compare proportion (cumulative incidence and incidence density) of patients developing (treatment-related) adverse events in each study group over the duration of the study, with special attention to infusion-related adverse events and infections. Furthermore, the cost-effectiveness of both ultra-low RTX doses and the conventional low dose are compared for the six-month study period. For prediction modelling, baseline factors (including RF/ACPA status, CD19+ B-cell count, serum RTX, serum anti-RTX) will be tested for associations with the outcome of DAS28-CRP low disease activity state at six months.

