### Interventions

Patients allocated to the standard low-dose group will receive a (blinded) single 1000 mg RTX infusion according to the standard protocol for infusion of rituximab. Patients allocated to the ultra-low-dose groups will receive 500 mg or 200 mg. This dose will be diluted to the same volume as the standard low-dose infusion to ensure the blinding of the study, all premedication and procedures are identical to the standard low dose. Of note, the possible advantage of shorter infusion times cannot be assessed in our study, because this would lead to patients and healthcare providers being unblinded.

It is aimed to leave all other rheumatic treatment unaltered as much as possible during the study period. However, all treatment decisions are left to the discretion of the treating physician and (changes in) use of paracetamol (acetaminophen), tramadol, non-steroidal anti-inflammatory drugs (NSAIDs), oral corticosteroids and DMARDs are all allowed during this study to ensure good care. During each visit, patients are asked about the use of these medications. Suggested treatment in case of clear loss of response is escape treatment with an extra dose of 1 × 1000 mg RTX. This can be done without unblinding, since the authorised dose of RTX is 2 × 1000 mg per six months and no patients will exceed this dose as the maximum study dose is 1 × 1000 mg.

We have determined several medication changes that are defined as ‘treatment failure’. These changes are: receiving an extra dose of RTX within the six-month study period; receiving another bDMARD (thus switching to another type of bDMARD); and using corticosteroids in a dose > 10 mg/day. Starting a concomitant conventional synthetic (cs)DMARD during the study period is not considered a treatment failure. The reasoning behind this is that all included patients will have received these csDMARDs before, with little effect on their RA, and the concomitant csDMARD is generally given as an adjuvant to increase the effectiveness of RTX.

In case of treatment failure, the patients will remain in the study, but the last measure of disease activity and other outcomes will be used as outcome employing a ‘last observation carried forward’ strategy.

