#### Assessments

At baseline, several characteristics of the patients will be measured, including demographics, disease and treatment characteristics. Also, possible predictors for response to ultra-low-dose RTX from peripheral blood will be collected, including (anti-)RTX drug levels and peripheral CD19 counts. Thereafter, visits will be performed at three and six months and when necessary in between (Fig. 1).

Several measures on disease activity will be collected during the study. The DAS28-CRP is a validated and widely accepted measure for RA disease activity and will be used as a primary outcome measure. It consists of four components: 28 tender joint count; 28 swollen joint count; CRP (mg/L); and patients VAS assessment of global disease activity (0–100) [26]. Remission is defined as DAS28-CRP < 2.4 and low disease activity by DAS28-CRP < 2.9 [32]. In addition, patient VAS assessment of pain, rheumatologist VAS assessment of global disease activity, acute phase reactants (CRP and ESR) and the OMERACT patient flare questionnaire are collected. To measure functioning of patients, the HAQ-DI, a validated instrument that is widely used in rheumatology is applied [33]. Quality of life is assessed using EQ5D-5 L, which is a validated instrument and comprises five questions and a visual analogue self-rating scale [34].

Adverse events are assessed at every visit during the study period and classified according to the Common Toxicity Criteria (CTC) [35]. In addition, we focus explicitly on infusion reactions and infectious events. Patients are asked to complete a short questionnaire after the RTX infusion on the occurrence of infusion-related adverse events. Medication use is charted using data from the electronic patient records on the use of DMARDs, corticosteroids and NSAIDs.

Costs will be calculated from a societal perspective. We will include the cost of outpatients’ clinic visits and telephone consultations, travel expenses for patients, costs of hospitalisation due to RA, costs due to health-related work absence and costs of medication during the six-month study period.

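### One six-month per-protocol set serves all four primary tests, so it can remove observed 3-month values from the 3-month tests and is not guaranteed to be conservative

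*Protocol article*

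**What the plan says.** Under Objectives, each ultra-low dose is compared with 1000 mg at two times, "compared to a pre-specified non-inferiority margin of 0.6 DAS28 points, at three and six months. Therefore, the study has four primary endpoints". The section on sample size and statistical analyses orders the four tests: "First, the non-inferiority of the 500 mg vs. 1000 mg at three months will be tested at" the two-sided 5% level, followed by 500 mg at six months, 200 mg at three months and 200 mg at six months, each conditional on the one before ("If this is statistically significant, then").

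The same section chooses the population: "Primary analyses will be done per protocol (PP), as this is the most conservative approach for a non-inferiority study". It then defines that population: "we will include patients who have received the study medication and completed follow-up of six months or until treatment failure", with the last disease activity value carried forward for failures. No separate definition is given for the 3-month tests. The other population is mentioned once: "In addition, analyses will be performed on an intention-to-treat basis (ITT").

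Under Assessments, "visits will be performed at three and six months and when necessary in between". Under Interventions, treatment failure means an extra rituximab dose, another biological, or corticosteroids above 10 mg/day; starting a conventional synthetic DMARD does not count. The rule for such patients reads: "In case of treatment failure, the patients will remain in the study, but the last measure of disease activity and other outcomes will be used". Leaving the study is not on the failure list.

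**The concern.** There are two separate difficulties.

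The first is timing. An analysis set for a 3-month endpoint should be settled by what is known at three months. Here it also requires six months of follow-up unless the patient has a listed failure. A patient seen at month 3 who leaves in month 5 has the value that the test needs and is still outside the set. This affects the test on which the other three depend.

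The second is the reason given for the choice. A per-protocol set tends to be conservative for non-inferiority when it removes deviations that blur a real difference between arms. Apart from undosed patients, this set excludes only people who do not complete follow-up without a listed failure. That is selection after randomisation on something that may be related to response. If patients who do badly leave more often on a lower dose, their removal moves the estimate towards non-inferiority.

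**Working it through.** **Does the definition remove observed 3-month data?** This needs no arithmetic. Take dosed patients with a 3-month DAS28-CRP:

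| Course after month 3 | In the per-protocol set? | 3-month value used? |
|---|---|---|
| Completes six months | Yes | Yes |
| Listed treatment failure | Yes, followed until failure | Yes |
| Leaves without a listed failure | No | No |

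The third row is the defect. It follows from the stated rule whatever one assumes about bias.

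**Is lost power the problem?** First, the plan's own figures, with baseline SD 0.7, margin 0.6, true difference 0, one-sided 2.5%, power 95% and 2:1 allocation:

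- r = 1 − SDchange²/(2 × 0.7²)
- control arm n = 1.5 × [0.7 × √(1 − r²) × (1.960 + 1.645)/0.6]²
- SDchange 0.9: r = 0.173, n = 25.7, rounded up to 26; 5 × 26 = 130
- SDchange 0.6: r = 0.633, n = 15.9, rounded up to 16; 5 × 16 = 80

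All four rows of Table 1 reproduce. (The factor 1.5 is 4.5/3 with 4.5 unsquared. The printed square does not reproduce the table, but that is a separate matter.) The drop-out allowance is 140 − 130 = 10, and 10/140 = 7.1%.

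Power per test at SDchange 0.9 is 96.4% with 28 controls, 95.2% with 26 and 93.6% with 24. At 0.6 it is 99.8% with 28 and 99.6% with 26. Losing the allowed number costs little power.

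**Could exclusion affect the type I error?** The article gives no leaving pattern, so this is an illustration under assumptions: 28 against 56 patients, SD of change 0.6, true difference exactly 0.6 (the boundary of the null), unadjusted t-test and 20,000 runs. In both arms a share d of patients worsening by more than 1.2 points leaves without a listed failure and is excluded.

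The proportion above 1.2 is 1 − Φ((1.2 − 0.6)/0.6) = 0.159 in the lower-dose arm and 1 − Φ(1.2/0.6) = 0.023 in the control arm. Overall drop-out is d × (56 × 0.159 + 28 × 0.023)/84.

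| d | Overall drop-out | Mean difference in those left | One-sided type I error |
|---|---|---|---|
| 0 | 0% | 0.60 | 2.5% |
| 25% | 2.8% | 0.57 | 4.1% |
| 50% | 5.7% | 0.54 | 7.5% |
| 100% | 11.3% | 0.46 | 20.5% |

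Repeat runs for the 50% row gave 7.2% to 7.5%. With all patients kept, the error stayed at 2.4% to 2.6%. The 25% and 50% rows lie inside the 7.1% allowance. The 100% row lies outside it and is shown only as an extreme. If leaving is unrelated to response, the two analyses estimate the same difference.

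**The case against.** The strongest reply is that the main route for informative loss is already closed. The article suggests an escape treatment for clear loss of response and says it can be given without unblinding. Patients who receive it, switch biological or exceed the corticosteroid limit count as failures, stay in the per-protocol set and keep their last observation. The study drug is a single infusion, so there is no continuing treatment to abandon. A patient who worsens, takes no listed drug and leaves is a narrow remainder. Keeping patients who start a conventional synthetic DMARD is a reasoned choice, and expected drop-out is small. All of this stands, and it limits how serious the point is.

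A second reply is that an article condenses the full protocol, and that populations per time point and the weighing of the two analyses may be set out there. This stands in part. It is why a reader who infers that the intention-to-treat analysis has no bearing on the conclusion goes too far: the article is silent on how the two are combined and says the report will follow the CONSORT extension for non-inferiority. But the six-month condition is a stated rule, and so is the claim of conservatism. Neither is a gap that a fuller document would merely fill.

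A third reply is that the bias figures are assumed. That is correct, and they are used here only to show that the claim of conservatism can fail.

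**Conclusion.** The point holds in two parts.

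1. **The 3-month tests.** As worded, the set removes dosed patients with a 3-month value who leave later without a listed failure. This follows from the text alone. At most 10 such values would be lost at the planned drop-out, and only if every drop-out came after month 3.
2. **The claim of conservatism.** It is not guaranteed for this set. In the illustration, the one-sided type I error is about 4% to 7% instead of 2.5% at 3% to 6% overall drop-out. That rests on the assumed leaving pattern, an SD of change of 0.6 and a true difference at the margin.

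A reader might infer that the primary analysis is biased towards non-inferiority. The document does not support this, because it says nothing about who will leave, from which arm or why, and listed failures are retained. A reader might also put a single size on the bias: 7% of a lower-dose arm leaving with a mean flare of 1.5 points, and no control losses, would hide 0.07 × 1.5 = 0.105 points, or 17.5% of the margin. That is one extreme scenario: 1.5 points is 2.5 times the planned SD of change, and the control arm is assumed to lose nobody. It should not be quoted as an expected effect.

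Power is not materially at issue.

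**What to change.** 1. Define the analysis set per time point. The 3-month tests should include every dosed patient with a 3-month DAS28-CRP or a treatment failure by then, whatever happens later. The six-month condition then applies only to the six-month tests.
2. Delete the statement that the per-protocol analysis is the most conservative, and claim non-inferiority only if the upper 95% confidence limit is below 0.6 in both the per-protocol and the intention-to-treat analysis. The second analysis protects only if it does not also drop patients who leave, so its handling of missing values should be fixed before unblinding.

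The cost is a few lines of wording, with no extra patients, visits or data. The downside is that requiring both analyses makes a claim slightly harder to reach. A repeated-measures model over both time points is an option, but the defect can be cured without it and the planned ANCOVA can stay.

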### Randomisation and blinding

Participants will be allocated to the treatment groups at a ratio of 1:2:2 (1 × 1000 mg vs. 1 × 500 mg vs. 1 × 200 mg). The experimental groups are larger than the control group to increase experience with the lower dosing and with the additional benefit that a larger number of potential predictive factors for response can be studies in multivariate prediction modelling in the ultra-low-dose RTX groups.

Randomisation will be performed using a computerised randomisation procedure and stratified to ensure equal distributions of two possible effect modifiers for response to ultra-low-dose RTX, concomitant conventional DMARD use and RF/ACPA status. Patients will be randomised using block randomisation in variable block sizes (multiples of 5) to more closely achieve the intended allocation ratio and to ensure that the allocation of participants will not be predictable. Patients, physicians, nurses, researchers and data analyst/statistician will be blinded for treatment allocation. The allocation is kept in opaque, sequentially numbered envelopes; envelopes are sequentially assigned by the pharmacist to each next patient. The infusions for the study will be prepared by the hospital pharmacy based on the randomisation number, the physical appearance of the three interventions will be indiscriminate (see below). Unblinding is expected to be rarely necessary (all patients receive RTX and retreatment with 1000 mg is allowed when necessary), but is possible after consulting the coordinating centres pharmacist.

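### The primary ANCOVA leaves out the two factors that stratify randomisation; if they predict outcome, its confidence intervals are slightly conservative, and including them is a nearly free improvement

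*Protocol article*

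**What the plan says.** Under Randomisation and blinding, the protocol article says that the computerised randomisation is "stratified to ensure equal distributions of two possible effect modifiers for response to ultra-low-dose RTX, concomitant conventional DMARD use and RF/ACPA status". Within strata it uses "block randomisation in variable block sizes (multiples of 5"), with a 1:2:2 ratio for 1000, 500 and 200 mg.

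Under Sample size considerations and statistical analyses it says: "The primary endpoints will be tested using 95% confidence intervals based on linear regression". The outcome is change in DAS28-CRP, with "dose group as determinant and baseline values of DAS28-CRP as covariate (ANCOVA". No section adds the stratification factors to this model. RF/ACPA status returns only as a candidate predictor of response. The sample size calculation credits a variance reduction to baseline DAS28 alone.

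There are four primary tests (two doses, at three and six months), and "multiplicity over the primary endpoints will be protected by a fixed testing procedure". On power: "we aim to have enough power for each at 95% for an NI margin of δ = 0.6".

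**The concern.** Blocking within strata balances the two factors across the dose groups, so variation between strata largely drops out of the dose contrast. A model without the strata still counts that variation as residual error. If the factors predict outcome, the reported standard error is then larger than the true sampling error of the estimate, and the interval covers more than 95%.

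Non-inferiority is read from the upper confidence limit against 0.6. The control arm has only 28 of 140 patients, and one failure in the fixed sequence stops the later tests, so avoidable width deserves a look.

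The primary analysis set is also per protocol. Exclusions after randomisation can disturb the balance that stratification achieved. Covariate adjustment guards against that for these two factors; the stated model does not.

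**Working it through.** **1. Reproducing Table 1.** Inputs from the sample size section: margin 0.6, true difference 0, two-sided 5% level, 95% power, baseline SD 0.7, 2:1 allocation within each comparison.

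- Correlation: r = 1 − SDchange² / (2 × 0.7²). For SDchange 0.9, r = 1 − 0.81/0.98 = 0.173. For 0.6, r = 1 − 0.36/0.98 = 0.633.
- (1.960 + 1.645)² = 12.995.
- Two-arm total = 4.5 × 12.995 × 0.49/0.36 × (1 − r²). This is 77.2 for SDchange 0.9 and 47.7 for 0.6.
- A third of that is 25.7 → 26 controls (trial total 130), and 15.9 → 16 controls (trial total 80).

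The rows for 0.7 and 0.8 give 20/100 and 24/120. All four rows match. They use a multiplier of 4.5; the article prints it squared, which is a separate matter. The stated overall power also reproduces: 0.95⁴ = 0.81.

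**2. Half-width of the planned interval.** With 140 patients (28:56:56) and SDchange 0.9:

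- Residual SD = 0.7 × √(1 − 0.173²) = 0.689.
- SE = 0.689 × √(1/28 + 1/56) = 0.689 × √(1.5/28) = 0.1596.
- Half-width = 1.978 × 0.1596 = 0.316 (t on 136 degrees of freedom).

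**3. Half-width with the factors in the model.** Let R² be the share of residual variance that they explain. The documents give none, so 0 to 0.10 is assumed. The SE is multiplied by √(1 − R²), with two more degrees of freedom used if both factors are binary.

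| R² (assumed) | Planned | With factors | Planned is wider by |
|---|---|---|---|
| 0 | 0.316 | 0.316 | 0% |
| 0.05 | 0.316 | 0.308 | 3% |
| 0.10 | 0.316 | 0.299 | 5% |

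**4. Simulation of the stratified design.** N = 140, 1:2:2, blocks of 5 or 10 within four strata, SDchange 0.9. Further assumptions: binary factors with prevalences 0.70 and 0.75, equal contributions, no dropout. There were 4,000 runs for power (true difference 0) and 8,000 for type I error (true difference 0.6). Each cell shows the model without / with the factors.

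| R² | True SD of estimate | Mean half-width | One-sided type I error | Power |
|---|---|---|---|---|
| 0 | 0.159 / 0.159 | 0.316 / 0.316 | 0.024 / 0.025 | 96.2% / 96.2% |
| 0.05 | 0.156 / 0.156 | 0.316 / 0.308 | 0.022 / 0.025 | 96.5% / 97.0% |
| 0.10 | 0.154 / 0.154 | 0.317 / 0.300 | 0.021 / 0.025 | 97.0% / 97.6% |

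The Monte Carlo error of the type I figures is about √(0.025 × 0.975/8000) = 0.0017. The estimate is equally precise under either model, because the design already supplies the balance; only the reported standard error differs. A repeat simulation gave power gains of 0.3 points (R² 0.05) and 0.6 points (R² 0.10).

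**5. The expected case.** At SDchange 0.6 with 28 controls the planned half-width is 0.248 and analytic power is 99.8%. Simulated power is 99.8% without the factors and 99.8 to 99.9% with them.

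**6. Over the sequence.** Multiplying four tests, as the article does for its uncorrelated worst case, R² 0.10 and SDchange 0.9 give 0.970⁴ = 0.885 against 0.976⁴ = 0.907. Positive correlation between the tests narrows that gap.

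**The case against.** The strongest reply is that nothing here is broken. The stated analysis is unbiased, its type I error is at or below nominal, and it cannot manufacture a non-inferiority claim. Power is already above 95% per test in the pessimistic case. All of that stands.

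A second reply is that the article calls the factors possible effect modifiers, which is not the same as calling them prognostic. A modifier changes the dose contrast; main-effect terms gain precision only if the factor explains outcome. This stands in part. Modification of response to the ultra-low doses, which four in five patients receive, would be expected to leave some association with outcome, but the article neither claims nor sizes one.

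A third reply is that a condensed article may leave such terms to a SAP. This does not carry the point. The article states outcome, determinant and covariate of the primary model, and that model does not match the stated randomisation.

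A reader might infer more than the documents support:

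- *That the intervals certainly are too wide.* With R² = 0 nothing is lost, and no R² is given.
- *That the omission throws away R² × 140, or 7 to 14 patients at R² 0.05 to 0.10.* This counts precision that stratification already gives the estimator (step 4), so that equivalence should not be used.

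**Conclusion.** The mismatch between design and model is in the text. Its consequence is conditional and small: over an assumed R² of 0 to 0.10, at most 0.017 DAS28 points of half-width against a margin of 0.6. A non-inferiority conclusion from the planned model would not be in doubt on this ground. The figures rest on the assumed R², binary factors and the simulated prevalences; the largest losses also need the pessimistic SD of change of 0.9. This is a minor improvement in consistency and efficiency, worth making because it costs almost nothing.

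**What to change.** Before unblinding, pre-specify one primary ANCOVA for all four tests: change in DAS28-CRP on dose group, baseline DAS28-CRP, concomitant csDMARD use and RF/ACPA status, the last two with the levels used at randomisation. State those levels, since the article does not define the categories of RF/ACPA status.

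The cost is one line of text and a few degrees of freedom (two if both factors are binary). No new data are needed, because both factors are known at randomisation. Fixing the model in advance also removes any later choice between an adjusted and an unadjusted result.
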